### Maternal measurements

Resting HR and blood pressure will be assessed before and after each exercise session and exercise HR will be monitored throughout exercise duration to maintain individual THR zones. Maternal morphometric measurements of weight, height, body mass index, skinfolds, and circumferences will be assessed prior to the start of exercise every 4 weeks beginning at the 16^th^ week of gestation.

Serum lipid profiles will be assessed pre- and post-intervention. Blood samples will be acquired from the antecubital or cephalic vein into 1 tiger and 1 purple topped BD Vacutainer SST. After centrifugation, plasma and serum samples will be stored at −80 C° until analysis. Serum samples will be thawed overnight prior to analysis of total cholesterol and high density lipoproteins (HDL) cholesterol using a clinical blood analyzer (Beckman Coulter, version 5.3.05). All values will be measured as milligrams per deciliter (mg/dL).

Body mass index will be calculated using BodyComp software (Version 3.05). As determined by the ACSM [29], a pre-pregnancy body mass index of 18.5-24.9 will be used for the normal weight classification, 25.0-29.9 for the overweight classification, and 30.0-34.9 for the obese class I classification. Weight and height at each measurement time will be assessed in typical, casual athletic clothing without shoes. Weight will be measured in pounds to the nearest 0.1 lb on a calibrated medical scale. Height will be measured in inches to the nearest 0.25 in. Gestational weight gain will be recorded in pounds to the nearest 0.1 lb as the difference in weight during the intervention period.

Skinfold measurements will be assessed at four sites (triceps, subscapular, suprailiac, and thigh) with Harpenden skinfold calipers every 4 weeks, starting at 16 weeks gestation. All skinfolds will be assessed on the right side of the body in a standing, relaxed state according to standard ACSM procedures [29]. All measurements will be taken to the nearest 0.2 mm, with the average of 2 trials taken. If the 2 trials are not within 2.0 mm, a third will be taken to ensure accuracy of measurement. The sum of the averages of the triceps, subscapular, and suprailiac folds will then be placed into the Durnin [40] equation to estimate percent body fat as validated in pregnant populations by Miller and Ballor [41].

Circumference measurements will be assessed every 4 weeks, starting at 16 weeks gestation, using a Gulick measuring tape. All measurements will be recorded in inches to the nearest 0.25 in., with the average of 2 trials taken. If the 2 trials are not within 0.5 in., a third will be taken to ensure accuracy of measurement. The minimum waist is measured as the smallest circumference between the umbilicus and the xiphoid process. Unilateral hips/thigh, mid-thigh, calf, arm, and forearm circumferences were also measured in inches in a rotational order according to the standardized procedures established by the ACSM [29].

### Fetal measurements

At 34 weeks gestation fetal weight, body morphometrics (i.e. circumferences and bone lengths), HR and HRV, and anatomical heart measures will be assessed using fetal ultrasound during a scheduled visit at a local obstetrics clinic. All healthcare providers will be blinded to participants’ group allocation. Fetal weight is estimated in grams. Fetal morphometric measures of biparietal diameter, femur length, humerus length, head circumference, and abdominal circumference are measured in millimeters. Right and left ventricular diameters and widths are also measured in millimeters. Heart physiological measures are calculated for both the right and left ventricle based on anatomical measurements assessed in the ultrasound. Stroke volume, measured in milliliters is calculated by subtracting the end diameter in systole from the end diameter in diastole. Ejection fraction is calculated by dividing the stroke volume by the end diameter in systole and multiplying by 100 for a percentage. Cardiac output, measured in milliliters, is calculated by multiplying stroke volume and HR.

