These studies have focused primarily on maternal aerobic exercise training or self-reported physical activity [9, 10, 12, 13, 17], measuring fetal HR and HRV. A scarce amount of research exists regarding the effects of other training modes, such as resistance training or circuit training during pregnancy, on fetal health and development as well as any continued benefits for the neonate, especially with regards to cardiovascular development and function. Research to date has only determined that various modes of maternal exercise training do not present undue risk to fetal or neonatal development [2, 24–26].

The primary aim is to determine the effects of different modes of exercise training (aerobic, circuit, and resistance) throughout pregnancy on health until the first year of life. The study presented will control individual exercise programs of varying modes throughout pregnancy to assess the effects of each on fetal and neonatal health adaptations.

We hypothesize that we will find: (1) lower measurements of maternal resting heart rate, weight gain, and body fat composition in women as follows: aerobic trained group = combination training group < strength training only group < < control group; (2) lower fetal HR, and increased infant HRV, stroke volume & cardiac output at 34 weeks gestation, 1, 6, and 12 months postnatal when exposed to various modes of maternal exercise compared to fetuses of women in the control group with greatest differences in aerobic trained group = combination training group > strength training only group > control group; and (3) normalized weights with lower fetal and birth body fat measures (i.e. BMI, body fat percentage) of all exercising groups compared to controls.

The purpose of this paper is to present the design and methodology of the Enhanced Neonatal Health and Neonatal Cardiovascular Efficiency Developmentally (ENHANCED) by Mom pregnancy study.

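### The fetal stroke volume and ejection fraction formulas are wrong as written: a difference of diameters is called millilitres, and ejection fraction is divided by the systolic value

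*Protocol article*

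**What the plan says.** All the relevant text is in the protocol article under Fetal measurements, which describes the 34-week ultrasound.

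- Raw data: "Right and left ventricular diameters and widths are also measured in millimeters".
- Derivation: "Heart physiological measures are calculated for both the right and left ventricle based on anatomical measurements assessed in the ultrasound".
- Stroke volume: "Stroke volume, measured in milliliters is calculated by subtracting the end diameter in systole from the end diameter in diastole".
- Ejection fraction: "Ejection fraction is calculated by dividing the stroke volume by the end diameter in systole and multiplying by 100 for a percentage".
- Cardiac output: "Cardiac output, measured in milliliters, is calculated by multiplying stroke volume and HR".

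The article nowhere states a step that turns diameters into volumes. In the Background, hypothesis 2 predicts "lower fetal HR, and increased infant HRV, stroke volume & cardiac output at 34 weeks gestation, 1, 6, and 12 months postnatal" in the exercise groups relative to controls. Ejection fraction is not named in any hypothesis. The Statistical analysis section applies ANOVA, analysis of covariance and regression to the fetal measures.

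**The concern.** There are three faults in three consecutive sentences.

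1. Two diameters in millimetres are subtracted and the result is labelled millilitres. The section contradicts itself on units.
2. Ejection fraction is divided by the systolic value. The definition requires the end-diastolic value, because the fraction is the part of the filled ventricle that is ejected. With the systolic value below the line the result is not a fraction and has no ceiling at 100%.
3. Cardiac output multiplies the faulty stroke volume by heart rate, and its unit has no time in it.

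Correcting the unit label would not be enough. Volume grows roughly with the cube of diameter, so a diameter difference is not a rescaled stroke volume. It gives too little weight to heart size. If maternal training changes fetal heart size, the group contrast in stroke volume and cardiac output would be misstated in size and, in some configurations, in direction.

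**Working it through.** **Inputs.** From the article: diameters are in mm; SV = EDD − ESD, labelled mL; EF = 100 × SV / ESD; CO = SV × HR, labelled mL. EDD and ESD are the end-diastolic and end-systolic diameters. The article gives no fetal diameters, so every diameter below is assumed. There is no published figure to reproduce.

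**Units.** mm − mm = mm, so SV as printed is not in mL. If SV really were in mL, dividing it by a diameter in mm would give mL/mm, which is not a percentage.

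**Stroke volume against volume.** Two simple models are used: cube, V = D³/1000 mL, and sphere, V = (π/6) × D³/1000 mL, with D in mm.

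| EDD/ESD (mm, assumed) | SV as printed | Cube model (mL) | Sphere model (mL) |
|---|---|---|---|
| 12/8 | 4 | 1.22 | 0.64 |
| 15/11 | 4 | 2.04 | 1.07 |
| 18/14 | 4 | 3.09 | 1.62 |
| 16/10 | 6 | 3.10 | 1.62 |
| 20/15 | 5 | 4.62 | 2.42 |

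- The first three rows have the same printed value, while the volume differs by a factor of 1.62/0.64 ≈ 2.5.
- The last two rows reverse. The printed measure ranks 16/10 above 20/15 (6 against 5), and both volume models rank it below. Cube arithmetic: (16³ − 10³)/1000 = (4096 − 1000)/1000 = 3.10; (20³ − 15³)/1000 = (8000 − 3375)/1000 = 4.62.
- The reason is visible in the algebra. With r = ESD/EDD, the printed SV is EDD × (1 − r), whereas the cube volume is EDD³ × (1 − r³)/1000. If r is equal, both move the same way but at different rates: a uniformly 5% larger heart gains 5% as printed and 1.05³ − 1 = 16% in volume. A reversal needs size and shortening to change in opposite directions, as in the last two rows (r = 0.625 and 0.75).

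**Ejection fraction, diameters used as printed.** The printed value is (1 − r)/r. With the diastolic diameter below the line it would be 1 − r, which is fractional shortening. The cube-volume ejection fraction is 1 − r³.

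| r (assumed) | As printed | Fractional shortening | Cube-volume EF |
|---|---|---|---|
| 0.60 | 66.7% | 40.0% | 78.4% |
| 0.667 (18/12 mm) | 50.0% | 33.3% | 70.4% |
| 0.70 | 42.9% | 30.0% | 65.7% |
| 0.80 | 25.0% | 20.0% | 48.8% |

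The printed value matches neither alternative. It passes 100% only when r is below 0.5: 18/8 mm gives 10/8 = 125%. That case is extreme, since its cube-volume ejection fraction is 1 − (8/18)³ = 91%.

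**Ejection fraction, if volumes were meant.** A true fraction f becomes f/(1 − f): 40% becomes 66.7%, 50% becomes 100%, 60% becomes 150% and 70% becomes 233%. On this reading, every true value above 50% exceeds 100%.

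**Cardiac output.** At an assumed 140 beats/min, the three ventricles with a printed SV of 4 all give 4 × 140 = 560. The sphere model gives 89, 150 and 226 mL/min.

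**The case against.** The strongest reply is that these are slips of wording in a condensed article: diameter written for volume, and systole for diastole. The millilitre label suggests that a volume was intended, and the ultrasound software may supply volumes. That is possible, and it makes the miscalculation conditional on the text being applied as printed. But the article does not say so, and reading diameter as volume repairs stroke volume only. The ejection fraction denominator stays wrong, and on that reading impossible percentages become routine.

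Several limits on the reach do stand.

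- The formulas cover the 34-week scan only. Hypothesis 2 also names 1, 6 and 12 months, for which the article gives no formula.
- Ejection fraction is in no hypothesis, and the printed ratio keeps the rank order of fractional shortening. Its level, scale and mean differences are what change.
- The rank reversal is shown for two chosen ventricles that differ considerably in contraction (cube-model ejection fractions 76% and 58%). It shows that a group difference could reverse, not that one will.
- The article mentions diastolic and systolic diameters but does not say in which phase the widths are taken, so a formula using both may not be available.
- Allocation, intervention, raw data and the sample size calculation are unaffected.

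**Conclusion.** The point holds. As printed, the fetal stroke volume and ejection fraction formulas do not give the quantities they name, and cardiac output carries the stroke volume error forward. Stroke volume and cardiac output at 34 weeks belong to hypothesis 2, so this must be corrected before analysis.

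The unit contradiction and the wrong denominator follow from the text alone and need no assumption. The sizes depend on assumed diameters and on a cube or sphere model: a 2.5-fold spread in volume behind one printed stroke volume, and a printed ejection fraction of 25% to 67% where cubed diameters give 49% to 78% (r from 0.80 to 0.60). A wrong direction for a group difference is possible where heart size and shortening differ in opposite directions between groups, but it is not established.

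**What to change.** Restate the derived heart measures, for each ventricle:

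- Name one geometric formula that turns the measured dimensions into end-diastolic volume (EDV) and end-systolic volume (ESV). Use diameters and widths if both are recorded in both phases, otherwise a diameter-only model.
- SV = EDV − ESV, in mL.
- EF = 100 × SV / EDV, in %.
- CO = SV × HR, in mL/min.

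If no volume model is considered acceptable, report 100 × (EDD − ESD) / EDD under the name fractional shortening and drop the labels stroke volume and ejection fraction. That choice has a price: there would then be no fetal stroke volume or cardiac output, and those parts of hypothesis 2 could not be tested at 34 weeks.

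If the ultrasound software already supplies volumes, say so, name its method and correct the printed formulas.

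The cost is a text correction and recalculation from the diastolic and systolic diameters the scan already provides, with no new procedure. Only a formula that needs widths depends on those having been recorded in both phases, which should be checked first.

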## Discussion

Because of the increased popularity of various modes of training among pregnant women, it is essential to identify the health benefits to the fetus and neonate, especially regarding cardiovascular function and development. This study protocol is designed to assess the effects of varying exercise modes throughout pregnancy on maternal, fetal, and neonatal health outcomes. This study aims to address many unanswered questions by determining if various modes of exercise training throughout pregnancy provide different benefits to maternal, fetal, and neonatal health in normal weight, overweight, and obese women of varying pre-pregnancy activity levels. A better understanding on the effects of exercise training on fetal cardiovascular autonomic control and function and ensuing neonatal autonomic control, cardiovascular function, and body composition could have a profound impact on in utero fetal adaptations to stress and labor as well as the prevention and development of chronic diseases such as obesity, hypertension, and diabetes.

## Abbreviations

HR: Heart rate
HRV: Heart rate variability
RPE: Rating of perceived exertion
THR: Target heart rate
ACSM: American college of sports medicine
